**Information collected at triage station**			
	Demographics	ED root table	Age, gender, race, nationality, postal code
	ED-prehospital	ED triage	Mode of arrival, high priority (chest pain/suspected stroke case), fever or not
	ED–triage information	ED triage	Triage waiting time, triage class (Patient Acuity Category Scale system), time of the day (midnight or not), day of the week (weekend or not)
	Triage vital signs	ED vital signs	Pulse, respiration, SpO_2_^d^, systolic BP^e^, diastolic BP, temperature

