## Introduction

### Background

Across the globe, there is increasing demand for emergency department (ED) services [1,2]. Increased ED visits have resulted in overcrowding and long waiting times [3-5]. Furthermore, adverse patient outcomes have been reported, such as mortality [6], poor patient satisfaction, and high costs [7,8]. As the first layer of emergency care in an ED, triage plays an essential role in assessing and stratifying patients’ risks and ensuring that the critically ill receive appropriate emergency treatment promptly [9].

The triage process is commonly conducted by medical staff based on their own clinical experience, the patients’ symptoms, and basic information obtained from patients during their presentation to the ED. To make this critical step more objective, triage systems have been introduced. Some examples of triage systems include the 5-level Emergency Severity Index [10] in the United States, the Australasian Triage Scale [11] in Australia, and the Patient Acuity Category Scale (PACS) [12] in Singapore. They are simple and easy to use but subjective and static. These scores are based on symptoms, but many critically ill patients may not have apparent symptoms when they arrive at the ED and their conditions deteriorate rapidly during their stay in the hospital. To address this limitation, more dynamic and accurate risk prediction tools are required for better patient monitoring throughout the ED journey [13].

In response to this gap of needs, researchers are interested in developing multivariable predictive models and clinical scores to identify patients in the ED at risk of adverse outcomes such as admission [14,15], death [16], cardiac arrests [17], and intensive care unit (ICU) admission [18]. Models such as these are primarily based on patient information, vital sign instability, changes in laboratory results, and administrative records. However, some parameters may appear similar between high-risk patients and other patients during an ED visit, making the prediction models less accurate.

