### Variable Construction

Candidate variables have been identified based on expert opinions as well as relevant literature [18,30,34-36]. Moreover, we have sought input from clinicians and informaticians familiar with the raw data to determine which features are feasible to extract and construct from the sources. The general rationale is to include all ED-relevant variables of high quality. Therefore, irrelevant, repeated, or largely missing variables will be excluded. For time-series data (such as laboratory test results and vital signs), the first, last, and average measurements are extracted and constructed for each ED episode. Past health care utilization will be derived per the patient’s medical history.

Table 1 presents a list of high-level constructed variables. These variables are classified into 6 main categories depending on the time frame during which the variables could be collected: past medical history, ED triage, ED disposition, within the first 24 hours of inpatient stay, inpatient discharge, and after inpatient discharge. Variables of patient data include demographics, comorbidities, drug history, presenting vital signs, essential laboratory results, and treatments administered in the ED. There are also nonpatient variables such as ED waiting time from triage to consultation, ED boarding time (from consultation to ED disposition), patient load in the ED (number of other patients registered in the ED at that time), time of the day, and day of the week.

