### Outcomes

The clinical outcomes in this study include the following adverse events experienced by patients during their inpatient stay:

Admission: A hospital admission following an ED visit [37-39]. Each ED attendance is classified as admission or discharge according to the clinical decision made. As a result, patients who left before a decision could be made are excluded rather than considered discharged.Inpatient death: A clinically certified death of a patient admitted to the hospital and who died during the hospitalization.2/7/30-day mortality: A clinically certified death of an admitted patient that occurred 2/7/30 days after the ED visit regardless of the place of death.ICU transfer: Identified using the hospital’s admission, transfer, and discharge database. Whenever a patient had more than one transfer from ward to ICU, only the data before the first transfer were included.Cardiac arrest: Defined as the loss of a palpable pulse with attempted resuscitation in the ward.Prolonged hospital length of stay: Defined as 21 days or more for the hospital stay.

**Table 1 table1:** List of the high-level constructed variables in the master data set, along with their sources and categories.

Category	Subcategory	Source table	High-level variables extracted

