#### Proposed Method: Interpretable SERT

SERT consists of 3 scoring algorithms, each tailored to its application at different time points in the ED. On arrival at the triage station, SERT-1 is used to estimate patients’ likelihood of admission (inpatient and ICU) and 2-day mortality. SERT-1 is intended to assess the patient’s immediate urgency based on basic patient information, simple vital measurements, and medical histories readily available during triage. While in the ED, SERT-2 predicts patients’ admission (inpatient and ICU) and 2/7-day mortality using a variety of variables, including laboratory test results, vital signs, ED treatment, diagnosis, and some administrative information. As an extension of the SERT-1 algorithm, SERT-2 incorporates additional variables obtained during ED stay to better predict outcomes. On admission, SERT-3 predicts the likelihood of 7/30-day mortality, ICU transfer, and prolonged length of stay using variables collected in the ED and during the first 24 hours of inpatient stay. In actual clinical implementation, in the case where a patient has incomplete information, SERT will use imputation methods to fill in the missing values before calculating the risk score. In summary, SERT allows for a comprehensive risk assessment and prediction in the ED in a dynamic manner.

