The clinical risk-scoring models have been traditionally developed in 2 ways: through expert opinions or consensus and conventional cohort studies. However, both approaches are labor-intensive and are not easy to update over time. Recently, we developed an interpretable machine learning–based automatic clinical score generator, AutoScore, as a practical and universal solution for risk scoring [29]. Using the AutoScore framework, users could seamlessly generate parsimonious risk models (ie, point-based sparse risk scores), thereby supporting automated machine learning solutions in health care [43]. AutoScore comprises 6 modules. In module 1, random forest is used to rank variables in terms of their contribution to modelling. Module 2 categorizes continuous variables to address nonlinearity and facilitate the generation of point-based scores. Module 3 computes scores based on a subset of variables and logistic regression, while module 4 determines the optimal number of variables based on a parsimony plot. Module 5 enables fine-tuning of the cut-off values for categorizing continuous variables for preferable interpretation, and module 6 provides a final performance evaluation. AutoScore is used to develop the 3 SERT scoring algorithms with the candidate variables and the outcomes.

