#### Baseline Methods: Traditional Clinical Scores

Several traditional clinical scores will be calculated for performance comparison with the SERT scores. They are the PACS triage system [32], Modified Early Warning Score [44], National Early Warning Score [45], Rapid Acute Physiology Score [46], Rapid Emergency Medicine Score [47], and Cardiac Arrest Risk Triage [48].

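### PACS triage class is both an unexcluded candidate input to SERT and a comparator for SERT; if AutoScore retains it, the contrast with PACS shows only added value over PACS

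*Protocol article*

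**What the plan says.** All references are to the protocol article.

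- **PACS as a possible input.** Variable Construction states that "Candidate variables have been identified based on expert opinions as well as relevant literature" and presents Table 1 in the same section. It keeps good-quality variables relevant to the ED and drops those that are irrelevant, repeated or largely missing. Table 1, under information collected at the triage station, includes "triage class (Patient Acuity Category Scale system" in the same row as triage waiting time, time of day and day of week.
- **How the scores are built.** Proposed Method: Interpretable SERT says "AutoScore is used to develop the 3 SERT scoring algorithms with the candidate variables and the outcomes". Selection is empirical: "random forest is used to rank variables in terms of their contribution to modelling", and a parsimony plot then sets how many variables stay. The same section adds "As an extension of the SERT-1 algorithm, SERT-2 incorporates additional variables obtained during ED stay to better predict outcomes".
- **PACS as comparator.** Baseline Methods: Traditional Clinical Scores lists the scores to be compared with SERT: "They are the PACS triage system [32], Modified Early Warning Score [44], National Early Warning Score [45", followed by three more.
- **The stated weakness of existing triage.** Background says of triage systems, PACS among them: "They are simple and easy to use but subjective and static".

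No section excludes PACS from the predictors, and none plans a version of SERT without it.

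**The concern.** If a comparator is one of the terms in the score under test, the contrast has a narrower meaning than its label suggests. A SERT-1 that contains PACS and is compared with PACS answers the question: do age, vital signs, history and the rest add discrimination once the PACS class is known? A reader of the results will probably take it to answer another question: does SERT discriminate better than PACS? The first can be yes while the second is no.

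Two consequences bear on the article's purpose. SERT-1 is meant for use on arrival at the triage station, but a version with a PACS term needs a PACS class first. It would also carry forward the staff judgement that the Background section criticises.

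The plan lets the ranking and the parsimony plot decide whether PACS stays. The meaning of the SERT-versus-PACS contrast could therefore differ between scores and between outcomes, and would be known only after the models are fitted.

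**Working it through.** **Step 1: does the text allow the overlap?** Three statements matter. PACS is in a predictor-type row of Table 1 (outcomes have rows of their own). The candidate variables feed AutoScore with no exception for PACS. PACS is a named comparator. Followed as written, the plan can produce a SERT score that contains PACS and is compared with PACS. It need not, because selection may drop PACS.

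**Step 2: can such a score win when SERT alone would lose?** The article gives no AUC for PACS or SERT and no power or margin for this comparison, so there is no figure to reproduce. What follows is an illustration with assumed AUCs.

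Model: two normally distributed markers with equal variances in patients with and without the event, and within-class correlation r.

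- Separation of one marker: d = √2 × z(AUC), where z is the standard normal quantile.
- Separation of the best combination: D² = (d₁² − 2·r·d₁·d₂ + d₂²) / (1 − r²).
- Combined AUC = Φ(D/√2).

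Worked case, PACS 0.75 and the other variables together 0.65:

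- d₁ = √2 × 0.6745 = 0.954; d₂ = √2 × 0.3853 = 0.545.
- r = 0: D² = 0.910 + 0.297 = 1.207, so AUC = Φ(0.777) = 0.781.
- r = 0.3: D² = (1.207 − 0.312)/0.91 = 0.983, so AUC = Φ(0.701) = 0.758.

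With PACS held at 0.75 and the other variables worse than PACS throughout:

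| Other variables alone | Combined, r = 0 | Combined, r = 0.3 |
|---|---|---|
| 0.60 | 0.764 | 0.751 |
| 0.65 | 0.781 | 0.758 |
| 0.70 | 0.804 | 0.775 |

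In every row the score with PACS is above 0.75, while a score without PACS would be below it. The apparent gain runs from 0.001 to 0.054.

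**Step 3: would gains of this size be visible?** The Results section gives about 1.8 million visits and 650,000 hospitalizations over 13 years. Spread evenly (an assumption), that is 138,462 visits and 50,000 admissions a year. The Hanley–McNeil variance of one AUC, A, is

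[A(1−A) + (n₁−1)(q₁−A²) + (n₀−1)(q₂−A²)] / (n₁n₀), with q₁ = A/(2−A) and q₂ = 2A²/(1+A).

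- Admission, A = 0.75, n₁ = 50,000, n₀ = 88,462: SE = 0.0014, 95% half-width 0.0028.
- With the Study Setting figures instead (120,000 visits, 36,000 admissions, so n₀ = 84,000): variance = 8,100/(3.024 × 10⁹), SE = 0.0016, half-width 0.0032.
- Rarer outcomes, on 138,462 visits: half-width 0.021 at an assumed 0.5% event rate (692 events) and 0.047 at 0.1% (138 events).

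For admission, a gain of 0.01 would stand well clear of sampling error. For rare outcomes, one year's separate intervals would often not resolve gains of the size in the table.

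**The case against.** The strongest reply is that the overlap is only potential. Table 1 is captioned "List of the high-level constructed variables in the master data set" and also holds outcomes and discharge items, so a listing there does not make a variable a predictor. PACS has to be in the data set in any case to be scored as a baseline. The description of SERT-1 inputs does not name PACS, and selection may drop it. This stands as far as it goes. A reader might infer that the comparison necessarily sets SERT with PACS against PACS alone; the documents do not support that. They also do not bar PACS, which is why the point is put conditionally.

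Second, a gain on held-out 2019 and 2020 visits by a score that includes PACS is a valid finding of better discrimination than PACS alone. This stands. A reader might infer that the comparison can show nothing of value about SERT against PACS, and that goes too far. Only a stand-alone or replacement reading lacks support, and the article states no formal superiority hypothesis.

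Third, a reader might infer that PACS routes patients within the ED, so drives admission and ICU decisions and lends SERT a circular signal. Study Setting ties routing to the need for resuscitation and the patient's condition and does not say that the PACS class decides it. Any such signal would also favour PACS as comparator. The point here does not rely on it.

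Fourth, SERT-2 and SERT-3 are used after triage, when PACS is legitimately known. This stands, and the fix leaves them alone apart from labelling.

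Fifth, the illustration treats a four-level scale as a continuous marker and weights it optimally, which a sparse point score will not do. It shows the direction and the possibility, not a forecast.

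**Conclusion.** The point holds in conditional form. PACS is listed with the candidate triage variables, is not excluded from the AutoScore inputs, and is a named comparator. Where it is retained, the SERT-versus-PACS AUC contrast estimates added value over PACS. It does not show that SERT alone discriminates better than the triage system the Background section criticises, and SERT-1 could not then be scored before PACS is assigned.

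The size is illustrative and rests on assumed AUCs and the binormal model: with PACS at 0.75 and the other variables at 0.65, the combined score reaches about 0.76 to 0.78 for r between 0.3 and 0. A win of 0.01 to 0.03 would then coexist with a PACS-free SERT that loses by 0.10. For admission, a difference of that order would look conclusive in one test year.

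Severity is moderate. One of several comparisons is affected. Those with the other five clinical scores and the machine learning baselines do not suffer from this nesting, and development of the scores does not depend on it.

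**What to change.** For the comparison with PACS:

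1. State whether PACS class is eligible for each SERT score.
2. Derive SERT-1 a second time with PACS removed from the candidate list, and report both versions against PACS on the 2019 and 2020 test cohorts.
3. Label the result for the version with PACS as added value over PACS. Base any claim that SERT performs better on its own, or could replace PACS, on the PACS-free version.
4. PACS may stay in SERT-2 and SERT-3. Where it is retained, label the contrast with PACS as added value there too.

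If selection drops PACS from SERT-1 for an outcome, saying so settles the matter for that outcome.

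The cost is one extra AutoScore run per SERT-1 outcome on data already extracted, and probably a slightly lower AUC for the PACS-free score. The article reports that data were still being linked and cleaned, so on that account the choice could be fixed before results are seen.

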**Information collected at ED disposition**			
	ED vital signs	ED vital signs	Vital measurement frequency and major ED vital readings: pulse, respiration, fraction of inspired oxygen, SpO_2_, systolic BP, diastolic BP, temperature, pain level scale, Glasgow coma scale, alert (extracted from physical notes)
	ED laboratory	ED laboratory	Laboratory measurement frequency and major laboratory test results: potassium, creatinine, sodium, bicarbonate, albumin, creatine kinase-MB (mass), creatine kinase, prothrombin time, N-terminal pro–B-type natriuretic peptide, C-reactive protein
	ED consultation and treatment	ED consultation, ED treatment	Services provider, consultation waiting time, ED location, length of consultation, resuscitation, major emergency surgeries, pre-selected major ordering
	ED allergy	ED allergy	Major allergy types and reasons, severity
	ED disposition and diagnosis	ED disposition, ED diagnosis	Disposition type, major primary diagnosis, secondary diagnosis (eg, trauma)
	Outcomes	ED disposition, ED root table	Admissions, mortality within ED, direct transfer to ICU

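### SERT-2 is to predict admission during the ED stay, but its inputs are dated at disposition, with no cut-off before the admission decision

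*Protocol article*

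**What the plan says.** The section Proposed Method: Interpretable SERT places SERT-2 in the ED stay. There it is to predict "admission (inpatient and ICU) and 2/7-day mortality using a variety of variables, including laboratory test results, vital signs, ED treatment, diagnosis, and some administrative information". It extends SERT-1: "SERT-2 incorporates additional variables obtained during ED stay to better predict outcomes".

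Outcomes defines the admission label by the decision itself: "Each ED attendance is classified as admission or discharge according to the clinical decision made".

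Table 1 sorts variables by when they could be collected. It has a triage block and then a block headed "Information collected at ED disposition", with nothing between them for the ED stay before the decision. The disposition block holds the ED vital signs and laboratory results (with measurement frequencies), consultation and treatment, and a row reading "Disposition type, major primary diagnosis, secondary diagnosis (eg, trauma". A separate Outcomes row in the same block contains admissions and direct transfer to ICU. Both rows name the ED disposition table as a source.

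Variable Construction says of time-series data that "the first, last, and average measurements are extracted and constructed for each ED episode". It also defines ED boarding time as the interval between consultation and disposition. The only exclusions it states are for variables that are irrelevant, repeated or largely missing.

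**The concern.** A score used before a decision should be built from data that exist before that decision. Here the decision is the outcome. Last values, averages and measurement counts taken over a whole episode can include readings made once the decision was already taken. A duration that ends at disposition is unknown until disposition. A diagnosis that Table 1 dates at disposition may be the one recorded with the decision.

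Disposition type is the sharpest case. It is not in the Outcomes row, yet it encodes the admission outcome. AutoScore first ranks variables by their contribution in a random forest, so a variable that carries the outcome would tend to be ranked high.

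At stake is the AUC of SERT-2 for admission and ICU admission. If post-decision information enters, that AUC overstates what the score can do in use. The comparison with PACS, which is assigned at triage, would also be unfair. The 2019 and 2020 testing cohorts would not expose the problem if their variables are built in the same way, because they would carry the same leakage.

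**Working it through.** The article states no AUC, sample size or power for this point, so there is no figure to reproduce. The check is a comparison of passages, followed by an illustration of size.

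**Step 1. Time of use against time of data.**
- Time of use: during the ED stay (Proposed Method).
- Target: "admission (inpatient and ICU) and 2/7-day mortality using a variety of variables".
- Inputs named: "including laboratory test results, vital signs, ED treatment, diagnosis, and some administrative information".
- Where Table 1 places current-visit ED laboratory results, non-triage ED vital signs, ED treatment and ED diagnosis: the disposition block.
- Cut-off for the time-series summaries: the ED episode, not a point before the decision.

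The stated constructions therefore allow SERT-2 inputs that run up to or past the event they predict. First values are not affected in this way. Last values, averages, counts, diagnosis and durations can be.

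**Step 2. Does any stated rule keep such variables out?**
- The exclusions in Variable Construction do not mention timing or variables that encode an outcome. *Repeated* could be stretched to cover disposition type as a duplicate of admissions. It does not reach the summaries, the counts or boarding time.
- The description of AutoScore refers to the candidate variables as a whole, with no list per score.

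No rule clearly blocks them.

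**Step 3. Size if disposition type were used.**
- Admission prevalence, from Results: 650,000 / 1,800,000 = 36.1%.
- AUC of a binary predictor = (sensitivity + specificity) / 2. If it agrees with the label in a share c of visits in both groups, AUC = (c + c) / 2 = c. For c = 1 this is 1.00, whatever the other predictors.
- For c below 1, disposition type was combined with an honest score in a simulation of 400,000 visits at 36.1% prevalence. The honest score x is normal with SD 1 in both groups, and its means differ by d = √2 × z(AUC), where z is the standard normal quantile. The combined score is d·x + ln(c / (1 − c)) when disposition type indicates admission, and d·x − ln(c / (1 − c)) otherwise. At c = 0.95 the added term is ln 19 = 2.94.
- Assumptions, not in the document: honest AUC of 0.70 to 0.85, and c of 0.90 to 1.00.

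| Agreement c | Disposition type alone | Combined, honest AUC 0.70 | Combined, honest AUC 0.85 |
|---|---|---|---|
| 1.00 | 1.00 | 1.00 | 1.00 |
| 0.99 | 0.99 | 0.994 | 0.997 |
| 0.95 | 0.95 | 0.969 | 0.983 |
| 0.90 | 0.90 | 0.936 | 0.964 |

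Even at 90% agreement the result mostly reflects disposition type rather than the honest score.

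**Step 4. Size of the timing effect without disposition type.** This depends on how many readings fall after the decision and how informative they are. The document gives neither, so no figure can be computed.

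**The case against.** Table 1 is a list of the master data set, not of predictors by score. It also holds outcomes and discharge items such as length of stay, and nobody would infer that length of stay predicts prolonged length of stay. The sentence on SERT-2 inputs does not name disposition type. The field has another evident use: the admission definition drops patients who left before a decision, which requires knowing how each visit ended. A condensed article may also leave candidate lists to a fuller document.

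Most of this stands, and it rules out a stronger reading. A reader might infer that SERT-2 uses disposition type and that its admission accuracy is circular. The article does not say so. Circularity and an AUC of 1.00 are conditional on that use. Two further inferences also fail:
- *None of the inputs would be available in use.* First values and early results would be. The Strengths section says scores can be updated as variables change, which fits running values to date.
- *All the clinical scores in the comparison are handicapped.* The article does not say when the early warning scores are calculated. The clear case is PACS.

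Nor does the article say that the diagnosis or the last reading always follows the decision, or that boarding time is assigned to SERT-2.

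What the objection does not answer is the timing. The article itself fixes the episode as the window for the summaries, disposition as the end of boarding time, and disposition as the date of the block. Those definitions conflict with the stated time of use; this is more than detail left to another document.

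**Conclusion.** The point holds as a timing fault with an unblocked leakage risk. For the SERT-2 admission and ICU-admission models, the stated constructions allow inputs fixed at or after the decision that defines the outcome. Disposition type is a possible input that nothing clearly excludes; it is not a documented one.

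The size is conditional. Disposition type would give an AUC of 1.00 if it matched the label exactly, and 0.936 to 0.997 for agreement of 90% to 99%, given an assumed honest AUC of 0.70 to 0.85. The bias from timing alone cannot be computed from the document. Admission is a common outcome, at about 36% of visits, so it is a substantial part of what SERT-2 would be judged on.

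For 2-day and 7-day mortality, disposition type is not the outcome. There the issue is only whether the inputs exist when the score is used.

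**What to change.** For the SERT-2 admission and ICU-admission models:
- Set a prediction time that precedes the disposition decision.
- Build first, last and average values, measurement counts, durations and diagnosis only from data time-stamped before it.
- State that disposition type and consultation-to-disposition time are not candidate predictors.
- Apply the same rules in the training, validation and both testing cohorts.

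For the mortality models these variables may stay if the score is declared for use at disposition.

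The cost is some re-extraction using time stamps, at a stage when Results says the data are still being linked and cleaned. The admission AUC will probably be lower, but it will describe the score as it would be used.
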